#### Cost-effectiveness outcomes

Quality-adjusted life years (QALYs) will be assessed using the EQ-5D-5L^39^ at baseline (within 48 hours prior to surgery), at postoperative day 3 and postoperative day 30. Additional outcomes used for cost-effectiveness analysis include hospital bed days and admission costs (including equipment and consumable use), and unplanned hospital readmissions up to 28 days post-surgery (as per the Australian Commission for Safety and Quality in Health Care definition).^40^

### Data collection

#### Hospital data

For each month of the trial, a random sample of patient medical records, corresponding to 10% of monthly surgical cases (of between 59 and 226 health records), will be reviewed at each site currently in the control or intervention period. Random sampling will be stratified by duration of surgery (10%, ≤30 min; 30%, 30−60 min; 60%, ≥60 min). Outcome evaluators will extract data from patient records and hospital data sets (as outlined in table 1). Data will be recorded using structured data collection forms via REDCap (Research Electronic Data Capture) hosted on a secure drive. Patients will be assigned a unique study ID for de-identification and the purpose of linking data sets.

Hospital admitted data will include age (in years), sex, body mass index calculated by the most recent weight and height (within 3 months), comorbidities (using International Statistical Classification of Diseases, 10th Edition, Australian Modification referred to as ICD-10-AM classifications), American Society of Anesthesiologists’ (ASA) score, surgical specialty, mode of anaesthesia (general/spinal/epidural), urgency of surgery category and duration of surgery (in minutes from In Operating Room time to Out Operating Room time).

#### Patient-reported outcome surveys

Qualtrics will be used to distribute the quality of life tool (EQ-5D-5L^39^) at baseline, postoperative day 3 and postoperative day 30 via email or text message (as per the patient’s preference). On day 3, the follow-up survey will allow patients to indicate if their surgery did not proceed as planned, and the option to participate on their revised date of surgery. On day 30 the survey will also include the self-report wound infection survey,^31^ if patients indicate they have a wound.

#### Clinician and Site Implementation Team surveys

Electronic surveys and hard copy surveys will be distributed at each site pre-transition and post-transition period, with the assistance of departmental leads and assisted by site investigators.

#### Implementation activity logs

In collaboration with Site Implementation Teams, internal facilitators will maintain an activity log of all implementation activities including the number and role of participants, implementation strategy delivered and adaptations of planned strategy.

#### Participant follow-up

The subset of patients recruited to participate in data collection for PROs will be followed-up at 3 and 30 postoperative days for completion of the EQ-5D-5L^39^ and self-reported wound healing measures.^31^ For all other outcome measures from existing hospital data, data collection ceases at 30 days post-discharge for wound infection.

### Data analysis

#### Sample size determination and power

As recommended by Curran *et al*^41^ we have selected one co-primary aim in determining the required sample size: the clinical effectiveness outcome of perioperative hypothermia (table 1). The expected proportion of patients with perioperative hypothermia on PACU arrival at baseline is 0.274 (27%), based on a recent period prevalence study of five Australian hospitals.^2^ Minimum sample sizes were calculated based on the primary clinical outcome assuming unequal cluster sizes using a constrained randomisation approach.^29 30^ The use of constrained randomisation allows for site-specific sample sizes to represent a fixed proportion of their total surgical capacity, while aiming to minimise imbalance between the total sample sizes for control and intervention periods. For each month a site is in the control or intervention period, we will select a random sample of patients equal to 10% of monthly surgical cases, stratified according to the duration of surgery. Based on annual surgical numbers for participating sites, a 10% sample corresponds to 59–226 patients/site/month. To obtain at least 80% power, our proposed sampling strategy will detect a statistically significant and clinically relevant reduction from 0.274 (27%) in the control period to 0.2 (20%) in the intervention period. Calculations assume a 5% level of statistical significance, an expected intraclass correlation coefficient of 0.1. Across the constrained subset of possible randomisations, the total sample size for control and intervention periods combined will be between 12 732 and 14 100.

For the sample size, we have also considered the minimum detected increase in the primary implementation outcome. Given the lack of existing data on both monitoring and warming recommendations, we have used data on adherence to perioperative temperature monitoring at all recommended time points.^2^ Assuming that 2.7% of patients currently receive temperature monitoring at all recommended time points, with remaining parameters unchanged, we will be able to detect an increase from 0.027 (2.7%) in the control period to 0.1 (10%) in the intervention period with 82% power.

For the economic evaluation, a randomly selected subsample of up to 1500 patients will be directly recruited to complete PRO surveys, and prospectively followed-up (to allow for incomplete responses). This comprises an average of 300 patients per site over the 27-month trial duration. The sample size for the economic evaluation was determined based on the feasibility of directly recruiting participants with follow-up to 30 days post-surgery.

#### Primary analysis

The co-primary outcomes will be analysed using generalised linear mixed models (GLMM), assuming binary dependent variables. A random intercept will be defined for each site to account for clustering of observations under the stepped wedge design. Fixed effects will include intervention exposure (yes/no), calendar time to account for secular trends unrelated to the intervention (in months)^21^ and patient-level/surgery-level characteristics. The binary fixed effect for the intervention will estimate the expected within-site change in the co-primary outcomes associated with the intervention.

Associations between the dependent variable and fixed effects will be modelled using the logit link function. An identity link function will also be fitted as a comparison, to report risk differences. If the identity link function does not allow the model to converge, results for the logit link function will only be reported. Results for both unadjusted (except clustering) and adjusted analyses will be reported. Model parameters will be reported as estimated ORs (risk differences) with 95% CIs.

Subgroup analyses for the co-primary outcomes will examine intervention effects by sex, surgical specialty, type of anaesthesia, duration of surgery, elective/emergency, ASA classification I–V. A sensitivity analysis will also consider hypothermia defined at the following thresholds: <36°C, <35.5°C and <35°C.

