### Study design and setting

An incomplete stepped-wedge cluster randomised controlled trial design will address both aims. Stepped-wedge cluster designs allow all sites to begin implementation at different times, with each site acting as its own control.^21^
Figure 1 presents the trial design. Perioperative departments from five public hospitals in South East Queensland, Australia, will participate in the trial over 27 months (November 2023 to February 2026): three metropolitan hospitals (sized from 323 to 1054 beds) and two regional hospitals (from 438 to 738 beds). All hospitals provide elective and emergency surgery. Surgical specialties provided by sites include general surgery, orthopaedics, gynaecology, plastics and reconstructive, vascular, urology, maxillofacial, ear, nose and throat, ophthalmology. Two of the metropolitan hospitals provide neurosurgery, and one of these also provides specialist burns care. A random sample of patients undergoing surgery during the control or intervention period at each hospital will be included in the analysis. This protocol is reported according to the Standard Protocol Items: Recommendations for Interventional Trials statement^22^ and with reference to guidance for design and reporting of stepped-wedge cluster randomised controlled trials.^21^

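### The primary model's only random effect is a site intercept, so nominal coverage and the stated power rest on an unstated assumption that hospitals have no month-to-month variation of their own

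*Protocol article*

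**What the plan says.** The Primary analysis section of the protocol article sets out a generalised linear mixed model for both co-primary outcomes. Its random part is one term: "A random intercept will be defined for each site to account for clustering of observations under the stepped wedge design". The fixed effects are intervention exposure, calendar time in months, and patient and surgery characteristics. Time is shared by all sites, and the article does not say whether it is categorical or linear. The intervention coefficient is described as a within-site change. The one sensitivity analysis named there varies the temperature threshold, not the correlation structure. The Secondary analysis section models the secondary outcomes in a similar way.

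The Sample size determination and power section has the same structure: "Calculations assume a 5% level of statistical significance, an expected intraclass correlation coefficient of 0.1". No second correlation parameter is given. The claim is "To obtain at least 80% power, our proposed sampling strategy will detect a statistically significant and clinically relevant reduction", namely a "reduction from 0.274 (27%) in the control period to 0.2 (20%) in the intervention period". On sample size, "a 10% sample corresponds to 59–226 patients/site/month" and "the total sample size for control and intervention periods combined will be between 12 732 and 14 100".

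**The concern.** A lone site intercept makes two patients at one hospital equally correlated whether they are operated on in the same month or 26 months apart. Changes in staffing, equipment or local habits that move one hospital's hypothermia rate in some months and not others have no place in this model. A binomial model has no free residual variance to absorb them.

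The intervention effect is estimated from change within sites over time, which is where such variation sits. With five hospitals, one per sequence, little averages it out. If it exists, the reported standard error is too small, the intervals cover less than 95% and the test rejects too often. The article plans to disseminate the recommendations across Australia if benefit is shown, so a false positive on the primary outcome would matter.

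**Working it through.** **Inputs from the article.** Proportions 0.274 and 0.20 (difference 0.074); ICC 0.1; 5% significance, taken as two-sided; 59–226 patients per site per month; total 12 732–14 100; five hospitals over 27 months; a 6-month transition not analysed; intervention periods of 6 to 18 months; control periods starting in month 1 for clusters 1–3 and in months 4 and 7 for clusters 4 and 5.

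**Inferred or assumed.**
- Steps of 3 months (Figure 1 is not shown). Intervention months are then 18, 15, 12, 9, 6, and control months 3, 6, 9, 9, 9, giving 60 + 36 = 96 site-months.
- Site sizes 59, 82, 129, 204, 226. The three middle values are not given; this set returns exactly 12 732–14 100 over all 120 site orders.
- Any CAC below 1.

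**Method.** Generalised least squares on site-month means, a linear approximation to the logit model.
- Mean proportion: (0.274 + 0.20)/2 = 0.237. Total variance: 0.237 × 0.763 = 0.1808.
- Between-site variance: 0.1 × 0.1808 = 0.0181. Within: 0.9 × 0.1808 = 0.1627, divided by m for a site-month of m patients.
- With CAC below 1, the between-site variance splits into a constant part, CAC × 0.0181, and a site-by-month part, (1 − CAC) × 0.0181.
- Power = Φ(0.074/SE − 1.96).
- True type I error of the planned test = 2[1 − Φ(1.96 × SE_model/SE_true)]. SE_model is what the random-intercept model reports; SE_true is the actual standard error of the same estimator.

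**The plan's own figure (CAC = 1).** With categorical months the median SE is 0.0221, so power = Φ(0.074/0.0221 − 1.96) = Φ(1.39) ≈ 92%, with a range of 79–98% over the 120 orders. Other site-size sets matching the stated total range have minima of 76–80%. Linear time gives 98–99.6%. The claim reproduces.

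**Scale of the omitted variation.** At CAC 0.95 the site-by-month SD is √(0.05 × 0.0181) = 0.030, or 3 percentage points. Sampling SD of a site-month is √(0.1627/226) = 2.7 points in the largest site and √(0.1627/59) = 5.3 points in the smallest. A 3-point local fluctuation is thus of the same order as sampling noise.

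**Results, ICC 0.1, medians over 120 orders.** Type I error is for the planned model; power is for a model that includes the site-by-month term.

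| CAC (assumed) | Site-month SD, points | Type I, categorical | Type I, linear | Power, categorical (range) | Power, linear |
|---|---|---|---|---|---|
| 1 | 0 | 5% | 5% | 92% (79–98) | 99% |
| 0.98 | 1.9 | 9% | 9% | 83% (72–92) | 96% |
| 0.95 | 3.0 | 14% | 16% | 72% (62–80) | 89% |
| 0.90 | 4.2 | 22% | 25% | 57% (51–63) | 75% |
| 0.80 | 6.0 | 33% | 37% | 40% (37–43) | 56% |

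Example, CAC 0.95 with categorical months: the true SE is 1.33 times the reported one, so type I error = 2[1 − Φ(1.96/1.33)] ≈ 14% and coverage is about 86%. The SE of the correct model is 0.0293, so power = Φ(0.074/0.0293 − 1.96) = Φ(0.57) ≈ 72%.

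**Lower ICC.** At ICC 0.02, type I error is about 7%, 8% and 12% at CAC 0.95, 0.90 and 0.80 with categorical months, and 7%, 9% and 13% with linear time. Median power with categorical months is 86%, 81% and 74%.

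**Check on the approximation.** A logistic simulation (600 runs each) gave type I error of 4%, 7%, 13% and 19% at site-month SDs of 0, 2, 3 and 4.2 points.

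**The case against.** A reader might infer that the intervals are too narrow and the power claim false as they stand. The documents do not support that. Under the article's single ICC the claimed power is met, and every adverse figure above needs a CAC that the article does not give.

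The power loss also depends on the form of time, which is left open. With linear time, every site order keeps 80% or more at CAC 0.95 (85–91%). Even with categorical months, 70% of orders do so at CAC 0.98. A lower ICC shrinks the loss further. These points stand and make the power conclusion conditional. They do not rescue the test: type I error is inflated at every CAC below 1 examined, and linear time makes it slightly worse.

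The model adjusts for patient and surgery characteristics, and sampling is stratified by duration of surgery. That removes the measured case-mix part of site-specific variation, and the figures above take no credit for it. Unmeasured staffing, equipment and practice effects remain.

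One might add that no small-sample method is named for five clusters. A condensed article may leave that to the analysis plan, so it is not part of this point. The random-effects structure is different, because the article states it outright.

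**Conclusion.** The point holds in conditional form. Nominal coverage and the stated power both require that hospitals have no time variation of their own beyond the common time effect and the adjusted covariates. The article neither states nor defends this. It is not an arithmetic error.

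If the assumption fails, the error runs in one direction, towards false positives. At ICC 0.1 the type I error is about 9% at CAC 0.98 and 22–25% at CAC 0.90, across the two forms of time. Whether power falls below 80% depends on the CAC, the ICC and the form of time: the median crosses 80% between CAC 0.97 and 0.98 with categorical months, and between 0.91 and 0.92 with linear time.

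These sizes rest on inferred 3-month steps, assumed middle site sizes, medians over all 120 orders (the constrained subset is not listed) and a linear approximation. They were computed for hypothermia on arrival in the recovery unit only. The implementation co-primary outcome uses the same model and shares the weakness, but its size was not calculated.

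**What to change.** - Add a random site-by-month effect to the co-primary models and to the secondary mixed models built the same way.
- Fit a structure in which within-site correlation decays with time as a sensitivity analysis.
- State whether calendar time is categorical or linear, and report power for that form over a range of CAC, for example 0.8 to 1.0, in place of the unconditional figure.

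**Cost.** Confidence intervals widen if the variation is real, and the stated power becomes less favourable. If there is no such variation, the added variance should be estimated near zero and little is lost. The change is to analysis wording and model code; no new data are needed.

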### Randomisation

Randomisation is defined at the site level, meaning that a cluster is defined by one hospital site. Each site will be subject to a variable control and intervention period, based on the randomisation order (figure 1). All sites will go through a fixed 6-month transition period at the end of their control period. During the control period, clusters continue with normal care. During the 6-month transition period, implementation by Site Implementation Teams will commence. The only data collected during the transition will be locally collected data by Site Implementation Teams used for implementation planning purposes. Sites will then switch to and remain in the intervention period of data collection until the end of the trial, between 6 and 18 months depending on randomisation order. To reduce data collection burden while maintaining adequate statistical power, an incomplete design will be used. This means that the sites randomised to clusters 1–3 will commence their control period in month 1. Clusters 4 and 5 will commence their control period in months 4 and 7, respectively.

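### Read literally, the planned unadjusted version of each co-primary result omits calendar time, which in this stepped-wedge design makes it a before-after comparison

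*Protocol article*

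**What the plan says.** All of the following is in the protocol article.

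- Primary analysis, clustering: "A random intercept will be defined for each site to account for clustering of observations under the stepped wedge design".
- Primary analysis, fixed effects: intervention exposure, patient- and surgery-level characteristics, and "calendar time to account for secular trends unrelated to the intervention", measured in months.
- Primary analysis, target of the exposure term: "The binary fixed effect for the intervention will estimate the expected within-site change in the co-primary outcomes associated with the intervention".
- Primary analysis, versions to be reported: "Results for both unadjusted (except clustering) and adjusted analyses will be reported". The next sentence adds: "Model parameters will be reported as estimated ORs (risk differences) with 95% CIs". Neither version is named as the primary result.
- Randomisation: "All sites will go through a fixed 6-month transition period at the end of their control period". The only data collected in the transition are local planning data. Sites then stay in the intervention period to the end of the trial, for 6 to 18 months. Clusters 1 to 3 start control data in month 1, cluster 4 in month 4 and cluster 5 in month 7.

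**The concern.** In a parallel-group trial an unadjusted result is harmless, because randomisation balances calendar time between arms. In a stepped wedge, exposure is tied to time by design. Here each site supplies control data first and intervention data later, so a model with only exposure and a site intercept credits the intervention with any change over time that would have happened anyway. The plan recognises that risk, since this is its stated reason for including calendar time.

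The parenthesis about clustering excuses only the site term. On its wording, calendar time falls away with the patient and surgery covariates. One of two reported versions of each co-primary result would then be confounded by construction, would carry the narrower confidence interval, and would stand beside the valid version with nothing to say which one counts. Secondary outcomes are to be modelled similarly, so the wording may carry over to them.

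**Working it through.** **Inputs from the protocol article.** Five sites and 27 months (Study design and setting). A 6-month transition, intervention periods of 6 to 18 months, and control starts in months 1, 1, 1, 4 and 7 (Randomisation). Risks 0.274 and 0.20, ICC 0.1, 5% significance, 59 to 226 patients per site per month, and total sample size 12 732 to 14 100 (Sample size determination and power).

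**Assumptions.** Steps of 3 months, since the design figure is not shown and (18 − 6)/4 = 3. A two-sided test. Either equal sites of 140 per month or unequal sites of 59, 120, 140, 160 and 226 in any order. The unequal set gives totals of 12 969 to 14 091, inside the stated range.

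**Schedule (months).**

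| Cluster | Control | Intervention | Site-months (control, intervention) |
|---|---|---|---|
| 1 | 1–3 | 10–27 | 3, 18 |
| 2 | 1–6 | 13–27 | 6, 15 |
| 3 | 1–9 | 16–27 | 9, 12 |
| 4 | 4–12 | 19–27 | 9, 9 |
| 5 | 7–15 | 22–27 | 9, 6 |

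This gives 36 control and 60 intervention site-months. Months 1–9 hold control data only and months 16–27 intervention data only. Only months 10–15 hold both.

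**The plan's own power figure.** Generalised least squares on site-month means with a site random intercept gives, for 0.274 against 0.20:

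- categorical month: 0.91–0.93 with equal sites, 0.81–0.96 across orderings of the unequal sizes;
- linear month: 0.97–0.99;
- no time term: above 0.999.

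The stated figure of at least 80% is consistent with a time-adjusted model. It is a lower bound and the individual site sizes are not given, so it cannot be reproduced exactly and does not show which model was used.

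**Calendar gap within sites.** For a site observed over a span of S months with a 6-month hole, the mean intervention month minus the mean control month is (S − 6)/2 + 6 = (S + 6)/2. Spans of 27, 27, 27, 24 and 21 give 16.5, 16.5, 16.5, 15 and 13.5 months. These gaps do not depend on the step length.

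**Drift absorbed without a time term.** With equal sites the estimate is in effect a weighted mean of the within-site differences, with weights c·t/(c + t) for c control and t intervention months:

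- weights: 54/21 = 2.571, 90/21 = 4.286, 108/21 = 5.143, 81/18 = 4.5, 54/15 = 3.6; sum 20.1;
- multiplier: (12.0 × 16.5 + 4.5 × 15 + 3.6 × 13.5)/20.1 = 314.1/20.1 = 15.6.

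The full calculation gives 15.62, and 15.2 to 16.0 across orderings of the unequal sizes. With linear or categorical month in the model it is zero.

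**Standard errors, 140 per site-month.** Mean risk 0.237 gives variance 0.237 × 0.763 = 0.1808 per patient. Without time, SE = √(0.1808/140/20.1) = 0.0080, or 0.80 points. The full calculation gives 0.80 without time, 1.80 with linear month and 2.20 with categorical month. In the least favourable ordering of the unequal sizes, categorical-month power of 0.81 implies 7.4/(1.96 + 0.87) = 2.6 points.

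**Illustration with no true effect and no time term.** The drifts are assumed.

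| Drift (points/month) | False effect (points) | Share of the 7.4-point target | False positives |
|---|---|---|---|
| 0.1 | 15.62 × 0.1 = 1.56 | 21% | 50% |
| 0.2 | 3.12 | 42% | 97% |

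For 0.1, z = 1.56/0.80 = 1.95. Reproducing the whole planned effect needs 7.4/15.62 = 0.47 points per month, about 12 points over 26 months.

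**Check on the logit scale.** In 500 simulated trials (140 per site-month, no effect, site fixed effects standing in for the random intercept), a drift from 27.4% to 25% gave OR 0.93 with 38% false positives. A drift to 22% gave OR 0.84 with 97%. With month in the model the ORs were 1.00 and false positives 4–6%.

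**The case against.** **The authors may have meant something else.** Calendar time is listed with a design purpose, apart from patient and surgery characteristics, so unadjusted could mean without those characteristics only. That is a reasonable reading, and a reader should not infer that the investigators have decided to drop calendar time. But the sentence names one exception, and the site random intercept is the term described as handling clustering. Nothing elsewhere in the article keeps time in.

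**The specified model is already right.** This stands. The adjusted model contains calendar time, and a linear trend does not bias it. A reader might infer that the trial's main result is confounded. The document does not support that, because only the companion result is affected and nothing in the article rests a conclusion on it.

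**This is detail for a fuller document.** A complete list of model terms could properly be left to one. Here, though, the article states the exception itself, in a form that does not suit the design.

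**The size is hypothetical.** This also stands. The article reports no secular trend, and with no drift the bias is zero. The multiplier comes from the schedule, whereas the drifts and individual site sizes are assumptions.

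**A crude estimate can be reported openly.** Agreed. The problem is an unlabelled one presented on equal terms, and a ban on any model without time would go beyond the defect.

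**Conclusion.** The point holds in a limited form. As worded, one of two reported versions of each co-primary result is a before-after comparison that takes in any secular trend at about 15 to 16 times its monthly rate. That version would also look two to three times more precise than the valid one: about 0.8 points against roughly 1.7 to 2.4, and up to 2.6 in the least favourable assumed ordering of site sizes.

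The multiplier must lie between 13.5 and 16.5 whatever the step length, if it is a weighted mean of the within-site gaps. Its narrower value, and the standard errors, rest on 3-month steps, ICC 0.1 and the assumed site sizes. The false-positive rate of about 50% rests in addition on an assumed drift of 0.1 point per month, and is an illustration rather than a forecast. The direction of bias follows the trend: falling hypothermia would flatter the intervention and rising hypothermia would hide its effect.

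The fault lies in the wording of a companion analysis and in the failure to name a primary version. It should be corrected before results are seen, but it does not undermine the time-adjusted analysis.

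**What to change.** In Primary analysis, and in the statistical analysis plan if there is one:

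- define the unadjusted model, better called minimally adjusted, as intervention exposure, calendar time and site clustering, omitting only patient- and surgery-level covariates;
- define the adjusted model as the same terms plus those covariates;
- name one of these time-adjusted models as the primary analysis for each co-primary outcome;
- if an estimate without calendar time is still wanted, label it crude and descriptive and draw no inference from it.

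The same definitions should apply to secondary outcomes that are modelled in the same way. The cost is a sentence or two of text, with no change to data collection, sample size or conduct.
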